## Abstract

**Background:**

Rural Australian adults are continually shown to be insufficiently active with higher prevalence of lifestyle-related diseases associated with physical inactivity compared to urban adults. This may, partly, be attributable to the challenges associated with implementing community-based physical activity programs in rural communities. There is a need for broadly accessible physical activity programs specifically tailored to the unique attributes of rural communities. The aim of the Rural Environments And Community Health (REACH) study is to evaluate the effectiveness of an online-delivered physical activity intervention for increasing regular walking among adults living in rural areas of South Australia.

**Methods/Design:**

This is a randomised controlled trial. The intervention is 12-weeks with a 12-month follow-up. Participants will be insufficiently active, aged 18 to 70 years and randomly assigned to either Control or Intervention group. Participants receive a pedometer, but only the Intervention group will receive access to the purpose built REACH website where they will report steps taken, affect and ratings of perceived exertion during daily walking. These variables will be used to establish individualised step goals for increasing walking. Control participants will receive a paper diary to record their variables and generic incremental step goals.

The primary outcome measures are time spent in sedentary, light and moderate-to-vigorous intensity physical activity, measured by accelerometry. Secondary outcomes include 1) health measures (anthropometric and physiological), 2) psychological well-being, 3) diet quality, and 4) correlates of physical activity (exercise self-efficacy and physical activity environments). Measures will be collected at baseline, post-intervention, 6-month and 12-month follow-up.

**Discussion:**

This protocol describes the implementation of a trial testing the effectiveness of an online resource designed to assist rural Australians to become more physically active. The outcomes of this study will guide the efforts of health promotion professionals by providing evidence for a relatively inexpensive, widely accessible and effective method for increasing physical activity that can be utilized by anyone with access to the internet. Findings may indicate future directions for the implementation of physical activity and other health related interventions in rural communities.

**Trial registration:**

Australian New Zealand Clinical Trials Registry:
ACTR12614000927628 (registered 28 August 2014).

## Background

More than half of Australia’s adult population does not participate in sufficient amounts of physical activity to infer positive benefits to health
[1]. Of particular concern are rural Australian adults, who are not only more likely to report being physically inactive
[1], but also suffer disproportionately from lifestyle-related diseases such as cardiovascular disease and type-2 diabetes mellitus
[2, 3].

Increasing physical activity provides an effective means of reducing one’s risk of lifestyle-related disease
[4–6]. Furthermore, evidence has consistently indicated that regular participation in physical activity benefits many other physiological outcomes (e.g. cardiovascular fitness, immune function, muscle strength and body composition), as well as improving psychological wellbeing (mood, self-esteem, depression and anxiety)
[7–9]. It is widely accepted that, to infer positive effects on health, adults should accumulate at least 30 minutes of moderate or vigorous physical activity on at least five days of the week
[10, 11]. More recently, recommendations of achieving at least 10,000 steps per day have gained significant momentum as an easily measureable indicator of sufficient physical activity
[5, 12].

Despite the well-documented benefits of physical activity for health, rural Australian adults remain less physically active than their urban counterparts
[1]. As much as 63% and 65% of rural men and women, respectively, do not report sufficient levels of physical activity, compared to just 55% and 60% respectively in major cities
[13]. In fact, according to Vaughan and colleagues
[14], as little as 25% of rural adults attain the recommended amounts of physical activity. This may be, in part, attributable to the challenges of implementing community-based physical activity programs in rural communities where accessibility to services and facilities can be limited
[15, 16]. As such, previous suggestions for improving physical activity levels in urban environments, for example cycling to work or walking to the local shops, may not be feasible in a rural setting. Similarly, rural infrastructure may not be conducive to physically active lifestyles, where common urban activities such as cycling to work may require individuals to share major arterials with high speed traffic and heavy vehicles. Thus, there is a need for safe and broadly accessible physical activity promotion interventions which are specifically tailored to the unique lifestyles and environments of rural Australian adults.

The purpose of this paper is to describe the protocol of the REACH (Rural Environments and Community Health) 12-week physical activity program, which has been specifically designed to test the effectiveness of an online-delivered walking intervention for increasing regular walking among adults living in rural areas of South Australia. The trial also aims to assess the effects of the walking intervention on markers of cardiovascular risk and to identify psychological, social and environmental predictors of a sustained response to the intervention. We hypothesise that the online delivered walking intervention will improve physical activity levels and improve cardiovascular risk profiles. We further hypothesise that psychological, social and environmental factors will predict longer term response to the online delivered walking intervention, both independently and interactively.

### Theoretical framework

The REACH intervention is based on Bandura’s
[17]
*social cognitive theory*. When applied to the context of physical activity interventions, social cognitive theory posits that interventions which include intrapersonal mediators (e.g. goal-setting, self-monitoring and self-efficacy), social mediators (e.g. family and peer support), and environmental mediators (e.g. access to facilities and opportunities) are most effective at eliciting a positive and sustained response
[18–20]. Furthermore, concepts from Locke and Latham’s
[21]
*goal setting theory* will be integrated into the intervention. This will be achieved by 1) developing *goal acceptance* (participants will be provided information regarding the importance of physically active lifestyles for health and wellbeing, thus, placing emphasis on achieving step goals); 2) incorporating *goal specificity* (step goals for the intervention group will be individualised, taking into account how they are feeling, their ability to achieve previous goals and physical capabilities); 3) providing *difficult goals* (step goals will be set high enough to provide a challenge and not be seen as too easy, but low enough to be attainable as to not discourage motivation); and 4) providing *feedback* (the REACH website graphs weekly step count averages to show changes over the 12-week program).

## Methods/Design

### Participants and setting

The REACH study is a randomised controlled intervention trial. Approximately 300 participants will be recruited from rural South Australia and randomised into either the Intervention or Control group. Table 
1 outlines the inclusion and exclusion criteria for the study. For the purposes of this study, ‘rural’ is defined as a Remoteness Area, identified by the Australian Bureau of Statistics (ABS), as predominantly outer regional, remote or very remote. The Riverland and Yorke Peninsula regions of South Australia have therefore been selected as recruitment regions. According to the ABS, 86.3% and 83.1% of the Riverland
[22] and Yorke Peninsula
[23] are classed as outer regional, respectively, satisfying the aforementioned criteria. The Riverland has an approximate population of 42,000 people
[22] and an average Socio-Economic Indexes for Areas (SEIFA) score of 914.14
[24], indicating an area of relative socio-economic disadvantage. The Yorke Peninsula has an approximate population of 27,500
[23] people and an average SEIFA score of 924.44
[24], indicating similar socio-economic disadvantage. The dominant employment sectors of these two regions are indicative of those associated with rural Australia, with the main employment sector in the Riverland being fruit and nut tree growing
[25], while dry land farming (crops and livestock) serves as the dominant employment sector in the Yorke Peninsula
[26].

**Table 1 Tab1:** **Inclusion and exclusion criteria**

Inclusion criteria	Exclusion criteria
• Aged 18-70 years	• Non-resident or resident <12-months of target regions prior to study start
• Self-reported resident of target regions for minimum of 12-months prior to study start	• Relocation of primary residence outside of the target regions during the study period (participants will be unenrolled from the study from that point on)
• Insufficiently active (engaging in fewer than 20 bouts of physical activity of at least 30 minutes) over the previous month	• Pregnant or intending to become pregnant during 12-month study period
• Access to the internet	• Physical or psychological condition (i.e. cognitive impairment) that may impede full participation in the study
• Deemed medically safe to participate in unsupervised moderate-intensity physical activity by satisfaction of stage one of the Adult Pre-Exercise Screening System (or review by an Accredited Exercise Physiologist)	
• Sufficient English language skills and cognitive ability to allow full participation in the study	
• Able to provide written informed consent	

### Study design

#### Recruitment and screening

Outline for the overall study protocol is presented in Figure 
1. Participants will be recruited via local newspaper advertisements, rural organisations (e.g. Country Women Association and SA Farmers Federation), local radio, school newsletters, local businesses and sporting/community clubs. Potential participants will initially be screened via telephone to determine eligibility. Eligible and willing participants will be provided with further information regarding the study and booked into an initial testing session. Written consent will be attained and pre-exercise screening completed during the initial testing session. Pre-exercise screening will be conducted using stage one of the Australian Adult Pre-exercise Screening System (APSS)
[27]. Stage one of the APSS is designed to identify individuals with signs or symptoms of underlying disease, or those who may be at high risk of adverse events during exercise. Any participants who answer “Yes” to any questions in stage one will be assessed by an Accredited Exercise Physiologist for suitability to participate in unsupervised moderate-intensity exercise.

**Figure 1 Fig1:**
[figure not shown]
**Outline of REACH study protocol.** Health measures include anthropometry, resting blood pressure, blood chemistry and cardiovascular fitness. Questionnaires include psychological well-being, diet quality, sleep quality, correlates of physical activity and demographics.

#### Randomisation and blinding

Participants will be randomised into either the Control or Intervention arm using a cluster randomisation technique. Participants with complex medical conditions will be reviewed by an Accredited Exercise Physiologist ([name]) and, if deemed to require increased monitoring, will be placed in the Intervention group for safety. It is not possible to blind key researchers ([name]) to participants’ group allocation as they will be performing information sessions prior to the intervention. Similarly, it is not possible to blind participants to group allocation due to the nature of the study design. Six other research assistants performing testing will be blinded to the participants’ group allocation.

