[10], how to setup and use their pedometer (Yamax DW700; Yamasa Tokei Keiki Co. Ltd., Tokyo, Japan) and tips for incorporating physical activity into daily life. The Intervention group, in addition to the information provided to the Control group, will be shown how to use the REACH website, including how to log their steps and other information. Measures will be repeated following the 12-weeks of the intervention period, and at 6-months and 12-months follow-up (i.e. 3-months and 9-months from end of the intervention). Participants will be recruited from three intervention regions: the Riverland; the Copper Coast (Upper Yorke Peninsula); and the Lower Yorke Peninsula. In each location, testing sessions will be provided in four different towns on different days. This is to minimise participant burden by providing a number of opportunities to participate around their usual schedule and reduce distances needed to travel. Testing will begin in the Riverland, followed by the Copper Coast and then the Lower Yorke Peninsula. Testing in the second and third regions will begin during the information session (session four) of the preceding region.

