### Statistical considerations

#### Sample size

A priori power calculations indicated 106 participants are required per group (n = 212) to detect a medium effect size (Cohen’s d = 0.5), at 80% power, with significance level set at α = 0.05 and the assumption that the predictors will contribute an R^2^ of 0.5. Given a 30% attrition rate from a recent pilot study (unpublished) a total sample size of 300 will be targeted.

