#### Statistical plan

Data will be collated and manipulated using Microsoft Excel 2010 (Microsoft Corporation, Redmond, WA). Statistical analyses will be performed using STATA Data Analysis and Statistical Software version 12 (StataCorp LP, College Station, TX) and SPSS version 21 (IBM corp., Armonk, NY). Significance levels will be set at α = 0.05. Distributions of all variables will be assessed using the Shapiro-Wilk test, with appropriate normalization procedures applied where required. Independent samples t-tests will be performed on baseline measures to test for differences in demographic outcomes. Change scores for all outcomes will be calculated and compared between randomisation groups using parametric or non-parametric analyses as appropriate for the data distributions. Random effects mixed modelling will be used with time (0, 12, 26 and 52 weeks) and group allocation (Intervention and Control) as the fixed factors. A time by group interaction term will be used to formally test the aims of the study.

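### Allocation is described as cluster randomisation, but neither the listed sample-size inputs nor the named analyses allow for clustering

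*Protocol article*

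**What the plan says.** Three sections of the protocol article bear on this.

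- **Randomisation and blinding:** "Participants will be randomised into either the Control or Intervention arm using a cluster randomisation technique". The unit of allocation, the number of clusters and their size are not given.
- **Sample size:** "A priori power calculations indicated 106 participants are required per group (n = 212") are needed "to detect a medium effect size (Cohen’s d = 0.5), at 80% power", with α = 0.05 and an R² of 0.5 for the predictors. The target is raised to 300 for 30% attrition. No ICC, cluster size or design effect is among the inputs.
- **Statistical plan:** change scores are compared between the randomised groups by parametric or non-parametric tests, according to distribution. A random effects mixed model takes time (four visits) and "group allocation (Intervention and Control) as the fixed factors", and their interaction is the formal test of the aims. No random factor is named, neither participant nor cluster.

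The Testing procedure section gives the only geographic structure. There are three regions, and "In each location, testing sessions will be provided in four different towns on different days". It does not say that towns or regions are units of allocation.

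**The concern.** When groups of people are allocated together, members of one group tend to resemble each other, and the variance of the between-arm difference grows by the design effect. An analysis that treats participants as independent then understates the standard error, and its type I error exceeds 5% at any positive ICC. A random effect for participant does not repair this. It handles repeated measures within a person, not variation between clusters in how people change.

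The allocation sentence describes one design, while the listed sample-size inputs and the change-score tests suit another. At stake are the between-group comparisons for all outcomes, including the primary accelerometer outcomes, and the power claim. Clustering is plausible here: recruitment runs through local clubs and businesses, information sessions are separate for each arm, and testing is staggered by region.

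**Working it through.** **1. The plan's own figure.** For two means, n per group = 2(1.96 + 0.8416)²/d². With d = 0.5 this is 2 × 7.849/0.25 = 62.8, so 63 (64 with the t distribution). If R² = 0.5 reduces the variance, n = 62.8 × 0.5 = 31.4, so 32. If it inflates the variance, n = 62.8/0.5 = 125.6, so 126. None of these is 106, so the stated figure is not reproduced and its basis is unknown. It exceeds 63 by a factor of 106/63 = 1.68, but the article does not present that excess as an allowance for clustering. The attrition step is roughly consistent: 212/0.7 = 303, against a target of 300.

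**2. Inputs for the cluster check.** From the article: 212 completers, d = 0.5, α = 0.05 (taken as two-sided), R² = 0.5. Assumed, because the article gives neither: ICC of 0.01, 0.02 or 0.05 for the quantity analysed, and 6, 12 or 24 equal clusters. Twelve would correspond to 3 regions × 4 towns if towns were the clusters.

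**3. Type I error if clustering is ignored.** With k clusters, m = 212/k and DE = 1 + (m − 1) × ICC. The true error is 2[1 − Φ(1.96/√DE)]. Example with k = 12 and ICC 0.05: m = 17.67, DE = 1 + 16.67 × 0.05 = 1.83, 1.96/√1.83 = 1.45, error = 14.8%.

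| Clusters | DE at ICC 0.01 / 0.02 / 0.05 | True error of a nominal 5% test |
|---|---|---|
| 24 | 1.08 / 1.16 / 1.39 | 5.9% / 6.8% / 9.7% |
| 12 | 1.17 / 1.33 / 1.83 | 7.0% / 9.0% / 14.8% |
| 6 | 1.34 / 1.69 / 2.72 | 9.1% / 13.1% / 23.4% |

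With 12 clusters, the effective number of participants, 212/DE, is 182, 159 and 116.

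**4. Power of a test that respects clusters.** In SD units, SE = √(4 × v × DE/212). Here v = 1 if R² is ignored, 0.5 if it reduces the variance and 2 if it inflates it, with the ICC unchanged. Power comes from the noncentral t with k − 2 df and noncentrality 0.5/SE. Example with k = 12, ICC 0.05 and v = 1: SE = √(4 × 1.83/212) = 0.186, noncentrality 2.69, critical value 2.228 on 10 df, power 68%.

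| 12 clusters, 10 df | ICC 0.01 | 0.02 | 0.05 |
|---|---|---|---|
| R² ignored | 86% | 81% | 68% |
| R² reduces variance | 99% | 98% | 93% |
| R² inflates variance | 58% | 52% | 40% |

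Ignoring R², power is 92%, 90% and 84% with 24 clusters, and 66%, 56% and 39% with 6.

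**The case against.** The strongest reply is that the trial may not be cluster-randomised at all. The allocation sentence has participants as its subject, and the abstract and the Participants and setting section speak of participants assigned or randomised to a group without mentioning clusters. Some individuals are allocated by review: "if deemed to require increased monitoring, will be placed in the Intervention group for safety". The word cluster may therefore be loose. This stands as a doubt about which sentence is wrong. It does not remove the conflict, because the sections cannot all be right as written.

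Three stronger readings are tempting, and the article does not support them.

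- **That every confidence interval and p-value is unreliable.** The plan calls for random effects modelling and does not name the random factors. A condensed article may leave these to a fuller plan, so a cluster effect in that model is not excluded. The firm criticism is of the change-score comparisons, which have no such provision.
- **That there are 12 clusters, or only 3.** Towns appear as testing venues, provided to reduce travel and fit people's schedules. Neither towns nor regions are called units of allocation.
- **That the trial is underpowered.** The 106 per group exceeds the unclustered requirement of 63 or 64, and the answer turns on cluster count, ICC and the role of R².

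Spare sample size does not, however, protect the type I error of a test that ignores clusters.

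**Conclusion.** The point holds, conditional on allocation being by cluster as stated. The listed sample-size inputs contain no allowance for clustering, and no named analysis does either. The change-score tests would then be anti-conservative, and so would the mixed model unless it carries a cluster effect. Over the assumed range of 6 to 24 clusters and ICC 0.01 to 0.05, the true error of a nominal 5% test runs from about 6% to 23%, with 7%, 9% and 15% at 12 clusters. The stated 80% power is not supported for this design, but whether real power is lower or higher is not established: at 12 clusters the three readings of R² span 40% to 99%. ICC, cluster count and equal cluster sizes are assumptions. The excess over 5% at any positive ICC does not depend on the particular values chosen.

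**What to change.** Reconcile Randomisation and blinding, Sample size and Statistical plan.

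If allocation is by cluster:

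- State the unit and the number of clusters.
- Put a random intercept for cluster in every between-group model, with Satterthwaite or Kenward-Roger degrees of freedom. In the repeated-measures model, let the cluster effect also vary over time, because a constant cluster effect cancels from the time-by-group contrast.
- If region enters as a fixed effect, count the degrees of freedom it uses. With 12 clusters, two region terms leave 8 df, and power at ICC 0.02 (R² ignored) falls from 81% to 79%.
- Drop the unclustered change-score tests as inferential analyses.
- Restate power at the planned n over a range of ICCs, and say how R² enters.

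If allocation is individual, correct the allocation sentence instead.

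The cost is wording and extra model terms, wider intervals and possibly a less favourable stated power. No extra participants are needed, because power is restated at the planned size rather than restored by recruiting more.

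### Participants judged to need increased monitoring go to the Intervention group without randomisation, and the plan has no provision to keep them out of the between-group comparison

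*Protocol article*

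**What the plan says.** The abstract of the Protocol article says that participants are "randomly assigned to either Control or Intervention group", and the section on participants and setting states: "The REACH study is a randomised controlled intervention trial". The section on randomisation and blinding opens in the same way: "Participants will be randomised into either the Control or Intervention arm using a cluster randomisation technique".

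That section then adds an exception. "Participants with complex medical conditions will be reviewed by an Accredited Exercise Physiologist" and, "if deemed to require increased monitoring, will be placed in the Intervention group for safety". The rule runs in one direction only. It rests on a judgement about health, and no limit or expected number is given.

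Under the statistical plan, change scores for every outcome are to be "compared between randomisation groups". A mixed model with time and group allocation as fixed factors follows, and its time-by-group interaction is the formal test of the study aims. The article does not say that directly placed participants are left out of this comparison, analysed separately or adjusted for.

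**The concern.** Randomisation justifies reading a difference between arms as an effect of the intervention. Here, one subset enters the Intervention arm because of its members' health, and the same rule keeps such people out of Control. If their activity, fitness or cardiometabolic measures change differently over the year for reasons unrelated to the website and calls, that difference is counted as an intervention effect.

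The direction cannot be foreseen. These participants might gain less in walking and fitness, which would mask a benefit. They might also start with worse blood pressure, lipids or glucose and move further toward the mean, which would exaggerate one. Different drop-out could act either way. The planned baseline t-tests concern demographic variables and would not correct any of this. Covariate adjustment would have to extrapolate, because the flagged subgroup has no counterpart in Control.

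The rule affects all primary and secondary outcomes. If these participants are not marked at enrolment, the purely randomised comparison may not be recoverable later.

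**Working it through.** **Inputs.** From the sample size section of the Protocol article: 106 per group (212 in total), d = 0.5, 80% power, α = 0.05 (sidedness not stated; two-sided assumed), 30% attrition and a target of 300. Not given anywhere, so assumed: the share *f* of the Intervention arm placed directly (2–20%), and *D*, their difference in mean change from the randomised participants (0.2–1.0 SD).

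**The plan's own figures.** The article gives no figure for the number placed. Its 106 per group is used below only as a group size. The usual two-sided formula at d = 0.5 and 80% power gives 2 × (1.96 + 0.842)² / 0.5² ≈ 63 per group, so 106 is not reproduced that way. It corresponds to about 95% power. The attrition step is close: 212 / 0.7 ≈ 303, against 300. The point does not depend on either check.

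**Step 1: the bias.** Let the randomised Intervention participants have mean change μ. The mean of the arm as analysed is

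(1 − f) × μ + f × (μ + D) = μ + f × D.

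Control contains no such participants, so the group difference is shifted by b = f × D. Sample size does not appear in this expression. As the sample grows the standard error falls and b stays, so b becomes larger relative to the standard error.

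**Step 2: effect on the test.** With 106 per group, SE = √(2/106) = 0.137 SD. The two-sided type I error is 1 − Φ(1.96 − b/SE) + Φ(−1.96 − b/SE). If the bias opposes a true effect of 0.5 SD, power is Φ((0.5 − b)/SE − 1.96).

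| f | D (SD) | b = f × D (SD) | b as share of d = 0.5 | Type I error | Power if bias opposes the effect |
|---|---|---|---|---|---|
| 2% | 0.2 | 0.004 | 0.8% | 5.0% | 95.1% |
| 5% | 0.5 | 0.025 | 5% | 5.4% | 93.3% |
| 10% | 0.5 | 0.05 | 10% | 6.5% | 90.6% |
| 10% | 1.0 | 0.10 | 20% | 11.3% | 82.9% |
| 20% | 1.0 | 0.20 | 40% | about 31% | 58.9% |

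Example, fourth row: b/SE = 0.10 / 0.137 = 0.73, and 1 − Φ(1.23) + Φ(−2.69) ≈ 0.109 + 0.004 = 0.113. Without bias, power at 106 per group is 95.4%.

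**Step 3: what a randomised-only comparison would cost.** Suppose *k* of the 300 are placed directly (*k* assumed). The randomised number per arm after 30% attrition is (300 − k) × 0.7 / 2.

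| k | Randomised | Per arm after attrition | Power at d = 0.5 | Recruits needed to keep 212 randomised completers (303 + k) |
|---|---|---|---|---|
| 6 | 294 | about 103 | 94.8% | 309 |
| 15 | 285 | about 100 | 94.2% | 318 |
| 30 | 270 | about 94 | 93.0% | 333 |
| 45 | 255 | about 89 | 91.6% | 348 |

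All figures are at the individual level and unadjusted. They make no allowance for the cluster randomisation named in the same section.

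**The case against.** The best defence is that an article often leaves analysis sets to a statistical analysis plan, and that the phrase about randomisation groups could be read as covering only those who were randomised. That reading is possible. But the point rests on an allocation rule that the article states, beside an analysis by group allocation that it also states. Nothing in the document separates the two.

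It can also be said that the effect may be negligible. This stands: at 2% and 0.2 SD the bias is 0.004 SD, and a 1 SD difference in change unrelated to the intervention would be extreme. Bias is nil if nobody is placed, or if those placed change as the others do. Differences in baseline level largely drop out of change scores and of the interaction term, so only differential change or drop-out matters.

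Some stronger readings are tempting, but the document does not support them:

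- **That the arms are not randomised groups at all.** Only the directly placed subset bypasses randomisation.
- **That Control can contain nobody with a complex condition.** Those reviewed and not judged to need extra monitoring are still randomised. Only the flagged subgroup lacks a counterpart.
- **That the eligibility criterion contradicts the placement rule.** Table 1 requires people to be "Deemed medically safe to participate in unsupervised moderate-intensity physical activity" but goes on to allow "or review by an Accredited Exercise Physiologist". Someone may be cleared for unsupervised walking and still be thought to need more contact, which in the Intervention arm is given by telephone and through the website. The two statements are in tension, not in conflict.
- **That those placed are known to differ on the outcomes.** This is plausible, since pre-exercise screening looks for signs of disease, but it is an assumption.
- **That the planned model relies on equal baseline means.** The statistical plan states no such constraint.

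**Conclusion.** The point holds in this form: as written, the plan mixes randomised and health-selected participants in the Intervention arm and then compares the arms by allocation. That the rule exists is certain. The size of its effect is not, because the article gives neither the share placed nor their difference in change. Over the assumed ranges the bias is 0.004 to 0.20 SD, at most 40% of the targeted 0.5 SD, and the type I error runs from 5.0% to about 31%. The direction is unknown. These figures assume 106 analysed per group, a two-sided 5% test, no covariate adjustment and no clustering.

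This should be corrected even though the low end is harmless. The article sets no cap on the number placed, recruiting more people does not dilute the bias, and all outcomes are exposed to it.

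**What to change.** - Record the physiologist's decision, and flag the participant, before allocation is made or revealed, so that the assignment cannot influence the decision. The article already puts pre-exercise screening at the initial testing session and the arm-specific information at session four, so this may need little change. It does not state when randomisation takes place.
- Define the primary analysis set as randomised participants only.
- Report directly placed participants as a separate, non-randomised cohort. Add them to the between-group comparison only in a labelled sensitivity analysis.
- Count only randomised participants toward the recruitment target.

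The cost is one enrolment field, a few sentences in the analysis plan and a small loss of analysable participants. If 30 of 300 were placed, about 94 per arm would remain after attrition, with about 93% power at d = 0.5 before any allowance for clustering. Keeping 212 randomised completers would need 333 recruits. How these participants are cared for is a matter for the investigators, and this change does not affect it.
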